### Endpoints

The present study aims to investigate whether taVNS can influence fatigue and the associated quality of life in patients with long covid. To achieve this, the following endpoints will be evaluated:

The primary endpoint is acceptance of taVNS in patients with a long stimulation duration, measured by the average daily stimulation duration.Secondary endpoints include the effects of taVNS on the MFI20, BDI, quality of life (SF36), and PCS-Score.

### Selection of patients and data collection

A total of 45 patients will be recruited and divided into three groups. Patients will be informed about the study through flyers and by their general practitioners, and will be provided with access to a website. Additionally, local support groups will be contacted and informed. On the website, questions regarding the inclusion and exclusion criteria will be asked anonymously, without data storage. At the end of the questionnaire, patients will be informed of whether they qualified for the study. In the case of study qualifications, patients will be provided with an email address where they can sign up to participate. Patients will be informed about the study aims and procedures by an investigator or certified medical professional. After obtaining written informed consent, data collection will be pseudonymized in the RedCap electronic case report form (eCRF) system of Ruhr-University-Bochum and will be General Data Protection Regulation (GDPR)-compliant. The RedCap system automatically randomizes patients into Verum-1, Verum-2, or Sham groups (n = 15 each). The patients will be instructed on how to use the simulator for 4 h per day, with at least 1 h of consecutive stimulation in the left ear. Patients will be asked to log all stimulation times manually in a diary. Because patients in the sham group will also receive the device’s user manual, which states that they should feel a tingling sensation in the ear, they will be instructed to use the highest stimulation intensity that is not perceptible to them. After adjusting the stimulation to this level, sham patients will receive a non-functional electrode that does not perform any stimulation. This approach is justified as the principle “more is better” does not apply to vagus nerve stimulation, and stimulation below the perception threshold could still, theoretically, have an effect.

### Patient and public involvement statement

Local support groups, regional long-term outpatient clinics, and general practitioners all participated in the study design. They were informed that the study would take place, and encouraged to disseminate this information among their patients and study flyers.

### Sample size calculation

The group size was based on the aforementioned studies on taVNS in other forms of fatigue [31,35,41], our aforementioned FatiVa study [42], and an ongoing similar study in the USA which enrolled 40 patients (NCT05630040). Recommendations for group size made in previous pilot studies were also considered [51,52]. Based on the expectation of the superiority of the two target groups (low- and high-threshold stimulation) of at least 5 and 10 MFI units, respectively, compared to the placebo (shift), and a type I error of alpha = 0.05, a total of 3 × 12 cases = 36 cases were deemed to be required to achieve a study power of 80% for the most important secondary endpoint, the MFI20 questionnaire. The mentioned numbers were secured with a safety margin of approximately 10%–20% (depending on the dropout rate), resulting in a total of 3 × 15 cases = 45 cases, if necessary. The calculation will be performed using the R Package “MultNonParam” [53].

### Data analysis

The two-sided p-value of Fisher’s exact test will be used to evaluate the difference between the three groups (primary outcome is an incidence rate with patients who exceed a usage-time-threshold). Additionally, the two treatment groups will be descriptively compared with the placebo group, and between themselves. The rationale to use Fisher’s exact test is to compare binary data between groups (in total three two-group comparisons). The rationale for the Kruskal-Wallis rank analysis of variance is to avoid the potential influence of outliers and to handle unknown data distributions (normally distributed data are not expected).

Since three tests (each group compared with each other) are performed and the threshold for the p-value was set at an overall (studywise) alpha of 0.05, then three tests result in an Bonferroni-adjusted (comparisonwise) threshold of p/ 3 = 0.017. p-values below this threshold denote a statistical significant difference.

Secondary outcome measures included the MFI20, BDI, SF-36, and PCS-score, which were modified similarly to the primary outcome measures. BDI, SF36 and PCSS are other secondary measures which will be analyzed descriptively. Since those parameters are continous rank-analses of variance (Kruskal wallis tests) will be used. Descriptive statistics, such as means, medians, quantiles, and respective case numbers of the available data, will be reported. The between-group contrast will be reported as the mean difference with 95% confidence intervals. Additionally, a nonparametric estimation of the group effect (shift) using the Hodges-Lehmann estimator shift will be provided.

Successful acceptance and compliance will be defined as achieved when the acceptance criteria (average taVNS for 4 h/day) are met by at least 80% of patients. A total of 45 patients will be enrolled, with 15 assigned to each of the three groups: “sham”, “Verum-1”, and “Verum-2.” The decision to have 15 patients per group was based on feasibility, as well as from influence by studies that examined noninvasive VNS for sleep deprivation, lupus, and Sjoegren’s syndrome. Furthermore, the selected sample size was aligned with the recommended sample sizes for feasibility studies [51,52].

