## Abstract

*Background*: Up to 80% of patients who develop coronavirus disease-2019 (Covid-19) infection subsequently experience long covid/post-covid syndrome. The World Health Organization (WHO) has estimated that >770 million patients have been infected with Covid-19 globally. Even if only 10% of these patients develop long covid, > 75 million patients will suffer for a long period. Among the various symptoms of post-covid syndrome, fatigue is common, affecting up to 60% of the patients. As observed in other viral infections, elevated levels of inflammatory cytokines may play a role. Transcutaneous auricular vagal nerve stimulation (taVNS) is a noninvasive method that modulates the immune system via the central nervous system and has shown promising effects in autoimmune diseases and improving fatigue. In this pilot study, we investigated the feasibility of daily taVNS in patients with long covid-related fatigue. Additionally, the effects of taVNS on fatigue and quality of life will be analyzed. *Methods*: A total of 45 adult patients with long covid associated fatigue syndrome will be enrolled in this study, and will be randomized to the above-threshold-stimulation, below-threshold-stimulation, or sham-stimulation arms, after being informed that they will feel the stimulation. The above-threshold-group will receive a 4-week-long left-sided cymba conchae taVNS with 25 Hz, 250 µs pulse width 28s/32s on/off paradigm for 4 h throughout the day. The below-threshold group will receive stimulation below the sensational threshold, whereas the sham group will receive no stimulation following application of a non-functional electrode. The daily stimulation protocol will be recorded either manually or using the provided app. Three well-established questionnaires, the Multidimensional-Fatigue-Inventory-20, Short-Form-36, and Beck-Depression-Inventory, and the newly established Post-Covid-Syndrome-Score will be completed both before and after 4 weeks of stimulation. *Discussion*: The primary endpoint has been set as the patients’ average daily stimulation time after 4 weeks, while secondary endpoints include the effects of taVNS on fatigue and Quality of Live (QoL). As a non-invasive treatment option, taVNS may be a notable alternative for patients with post-covid related fatigue. *Trial registration*: This study was approved by the local ethics committee (23/7798) and registered (DRKS00031974) (see supporting information files). *Ethics & Dissemination:* The ethical justifiability of this study was supported by prior research demonstrating the safety of taVNS. Patients will be recruited by general practitioners, and written informed consent will be obtained. All data will be pseudonymized for collection and storage. The study results will be published in peer-reviewed journals with the aim of providing evidence of the potential of taVNS in long covid management. The study will be conducted in accordance with the principles of the Declaration of Helsinki.

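### The primary endpoint is declared as average daily stimulation time, but only the share of patients above an unnamed usage threshold is tested, with a very conservative Fisher test at 15 per arm

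*Protocol article*

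**What the plan says.** The Abstract states: "The primary endpoint has been set as the patients’ average daily stimulation time after 4 weeks". The Endpoints section names the concept as acceptance of taVNS, "measured by the average daily stimulation duration". Both describe a continuous quantity.

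The Data analysis section describes something else: the "primary outcome is an incidence rate with patients who exceed a usage-time-threshold". On the test it says: "The two-sided p-value of Fisher’s exact test will be used to evaluate the difference between the three groups". It then explains that this means three two-group comparisons of binary data, each judged against a Bonferroni threshold of 0.017. No cut-off is given at that point.

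The last paragraph of the same section defines acceptance as achieved "when the acceptance criteria (average taVNS for 4 h/day) are met by at least 80% of patients". It does not say that this is the threshold in the Fisher test.

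The section also names Kruskal-Wallis tests and the Hodges-Lehmann shift estimate. It gives a rationale for Kruskal-Wallis next to the one for Fisher's test without naming an outcome. The only outcomes it then ties to Kruskal-Wallis as continuous are the secondary questionnaire scores.

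**The concern.** A mean in hours per day and a proportion of patients are different variables with different effect measures and tests. This is not detail that an article leaves to a fuller document, because the article itself fixes both versions.

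Three things are at stake. First, a reader cannot tell which between-arm result is the primary one. Second, the cut-off matters in this trial. The Study plan section says that patients can track when the 4 h target is reached and that the device turns off after 4 h of continuous stimulation, so values at or very near 4 h may be common. A rule that counts patients who *exceed* 4 h and a rule that counts those who *meet* it could then give very different proportions. Third, an exact test on a split variable with 15 per arm has little room to reach 0.017. The Discussion intends to use this pilot to inform expected adherence in a larger trial.

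**Working it through.** **Inputs from the protocol article.** 15 per arm, three arms, overall alpha 0.05 (Data analysis); 12 per arm as the required number before the dropout margin (Sample size calculation); target of 4 h/day and 80% of patients (Data analysis).

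**Inputs not in the article, hence assumptions.** The SD of stimulation time, the acceptance rates by arm and the shape of the usage distribution. The only power statement, 80%, is for the MFI20, so there is no power figure for the primary endpoint to reproduce.

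**Alpha.** 0.05 / 3 = 0.0167, which agrees with the stated 0.017.

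**What the Fisher test needs.** If 12 of 15 patients (80%) accept in one arm:

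- 12/15 vs 5/15: two-sided p = 0.0253, not significant at 0.0167.
- 12/15 vs 4/15: p = 0.0092, significant.

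**True size and power of one Fisher comparison.** With i and j acceptors out of n in the two arms,

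P(reject) = Σᵢ Σⱼ Bin(i; n, p₁) · Bin(j; n, p₂) · 1[p_Fisher(i, j) ≤ 0.05/3].

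- Size, n = 15: both arms at 80%, 0.24%; both at 50%, 0.56%. The nominal level is 1.67%. This needs no effect-size assumption.
- Power, n = 15: 80% vs 50%, 14%; 80% vs 40%, 30%; 80% vs 20%, 77%.
- Power, n = 12: 80% vs 40%, 23.5%.

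**Comparison with a rank test on hours per day.** Simulated Wilcoxon (Mann-Whitney) test, n = 15 per arm, alpha 0.05/3. In the first two models the better arm has 80% reaching the target. Figures vary by one or two points between simulation runs.

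| Assumed usage | Contrast | Rank test | Fisher |
|---|---|---|---|
| Normal shift | 1 SD | 54% | 24% |
| Normal shift | 1.2 SD | 72% | 39% |
| Normal shift | 1.5 SD | 90% | 64% |
| Same, all usage above 4 h capped at exactly 4 h | 1 SD | 38% | 22–24% |
| Same, capped | 1.5 SD | 82% | 64% |
| Acceptors all exactly at 4 h, arms differ only in share | 80% vs 40% | 38% | 30% |
| Acceptors all exactly at 4 h, arms differ only in share | 80% vs 20% | 77% | 76% |
| Acceptors at 4.0–4.3 h, others 1–3.9 h, arms differ only in share | 80% vs 40% | 29–30% | 30% |
| Acceptors at 4.0–4.3 h, others 1–3.9 h, arms differ only in share | 80% vs 20% | 70% | 77% |

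Under capping, the exact Fisher figure at 1 SD stays at 24%, because capping does not change who reaches 4 h; 22% is a simulated value. In the capped and exactly-4 h rows, a strict reading of *exceed* would count nobody as accepting.

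**The case against.** The strongest reply is that there is one endpoint, not two. The Endpoints section names acceptance as the concept and the average duration as its measurement, and the 4 h/day, 80% rule turns that measurement into a yes or no. Fisher's test suits a binary outcome, and a feasibility target on a proportion needs a binary variable. A reader might therefore infer too much from the word *contradiction*. That part of the reply stands: the article partly links the two, and a binary primary outcome would be legitimate if declared as such. It is not declared as such in the Abstract or under Endpoints, and the Fisher sentence does not point to the 4 h rule.

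A reader might also infer that the split costs about half the power. The article does not support a fixed figure. It gives no SD, effect or rates for stimulation time, and its own remark that normal data are not expected, together with the 4 h target, makes the normal-shift model doubtful. The loss can vanish, as the table shows. It can even reverse: if acceptors in the lower arm sometimes over-use (4–6 h), at 80% vs 30% acceptance the rank test has 17% power against 52% for Fisher.

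Finally, this is a pilot sized on feasibility, and nothing in it proposes to read a non-significant result as equal acceptance. That risk is one of later interpretation, not a stated plan.

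**Conclusion.** The point holds as an unreconciled primary variable. The article declares average daily stimulation time and tests the proportion above a threshold that it does not name where the test is specified, with *exceed* in one place and *met* in the other. As written, the declared variable gets no formal between-arm comparison.

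Without any assumption about the shape of the usage distribution, the Fisher test at 15 per arm is very conservative: a true size of about 0.2% to 0.6% for common acceptance rates of 80% to 50%, against a nominal 1.7%, and 30% power for 80% vs 40%. The loss relative to a rank test is conditional: large under a normal shift (54% vs 24% at 1 SD), smaller with capping at 4 h, little or none if arms differ only in the share clustered at or just above 4 h, and possibly reversed with over-use. It should be reported only as a range under stated assumptions. The change is worth making, but the defect does not undermine the trial.

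**What to change.** 1. In Data analysis, name average daily stimulation time (hours/day) as the primary between-arm variable. Compare the three arms with Kruskal-Wallis, then pairwise rank tests at 0.05/3, and report the Hodges-Lehmann difference in hours with its confidence interval. These methods are already in the plan for the continuous secondary outcomes; only the interval for the Hodges-Lehmann estimate needs adding.
2. Keep the proportion reaching the 4 h/day acceptance criterion as the feasibility criterion, reported per arm with an exact confidence interval and set against the 80% target. Do not use it as the between-arm significance test.
3. State the cut-off once and use the same wording throughout, so that *exceed* and *met* are reconciled.

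If the sponsor prefers the binary outcome as primary, the Abstract and Endpoints should say so and name the threshold. The conservatism shown above then remains and should be acknowledged.

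The cost is wording only; the same data are collected. As the study has started, the change should be dated and made before stimulation times are seen by arm. The downside is that the between-arm result is in hours, and hours above the target do not necessarily mean greater acceptance, so the proportion must still be reported alongside.

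### The pairwise Fisher tests on arms of 15 are valid but use only about a third of their allotted alpha; Boschloo's exact test would recover power, by an amount that depends on the final arm sizes

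*Protocol article*

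**What the plan says.** The Data analysis section of the protocol article settles every element needed for this check.

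- **Test:** Fisher's, taken two-sided, with its use described in these words: "exact test will be used to evaluate the difference between the three groups (primary outcome is an incidence rate with patients who exceed a usage-time-threshold". The following sentences make clear that this means pairwise tests.
- **Reason for the test:** only that the data are binary: "exact test is to compare binary data between groups (in total three two-group comparisons".
- **Alpha:** "the threshold for the p-value was set at an overall (studywise) alpha of 0.05". Dividing it over the comparisons gives the cut-off: "three tests result in an Bonferroni-adjusted (comparisonwise) threshold of p/ 3 = 0.017".
- **Decision rule:** "p-values below this threshold denote a statistical significant difference".
- **Arm size:** "A total of 45 patients will be enrolled, with 15 assigned to each of the three groups".

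The Sample size calculation section derives 12 per arm for the MFI20 and then adds to it: "The mentioned numbers were secured with a safety margin of approximately 10%–20% (depending on the dropout rate". Its 80% power refers to the MFI20 only. The article states no power for the Fisher comparisons. The only rate it gives for the binary outcome is the 80% acceptance target.

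**The concern.** Fisher's test conditions on the total number of patients who meet the usage threshold. This design fixes the arm sizes but not that total. With about 15 per arm, the conditional distribution has few attainable p-values, and the test can fall well short of its nominal level. That shortfall is separate from the Bonferroni correction: at an unadjusted 0.05 with 15 per arm, Fisher's largest true error is still only 0.018.

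What is at stake is power in the only inferential comparisons planned for the primary outcome. The article bases its 15 per arm partly on feasibility, so the choice of test is one of the few ways to gain power without more patients. Boschloo's test takes Fisher's p as its statistic but calibrates it over the unknown common rate. The reason the article gives for Fisher (binary data) applies to it equally.

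**Working it through.** **Inputs from the article.** Two-sided test, three pairwise comparisons, overall alpha 0.05, rejection when p is below the threshold, 15 per arm. **Assumed, because the article gives only the 80% target:** the acceptance rates used for power.

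**1. The plan's own figure.** 0.05/3 = 0.01667, printed as 0.017. It reproduces. The rounding has a small effect, so both values are carried below.

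**2. True error of Fisher's test, 15 vs 15.** Take all 16 × 16 outcomes (x, y). Let R be the set with two-sided Fisher p below the threshold. Then

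size = max over p of Σ over R of b(x; 15, p) · b(y; 15, p),

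where b is the binomial probability and p the common rate.

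- At 0.05/3: 0.00566, reached at p = 0.376 and 0.624. Unused share: 1 − 0.00566/0.01667 = 66%.
- At 0.017: 0.00671, because 15 vs 9 and 6 vs 0 (p = 0.01686) now count. Unused share: 1 − 0.00671/0.017 = 61%.
- Bonferroni bound on the studywise error: 3 × 0.00566 = 1.7%, or 3 × 0.00671 = 2.0%, against the 5% allotted.

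**3. Boschloo's test, 15 vs 15.** Enlarge R in order of Fisher's p for as long as the size stays at or below the threshold. The region ends at Fisher p = 0.0352, with size 0.0165 at either cut-off. It contains the Fisher region, so its power cannot be lower. Example: 13/15 vs 6/15 gives Fisher p = 0.021 and Boschloo p = 0.009.

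**4. Power at 0.05/3, 15 vs 15.** Power = Σ over R of b(x; 15, p1) · b(y; 15, p2).

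| Assumed rates | Fisher | Boschloo |
|---|---|---|
| 80% vs 30% | 0.526 | 0.680 |
| 80% vs 40% | 0.303 | 0.446 |
| 80% vs 50% | 0.144 | 0.243 |
| 80% vs 60% | 5% | 11% |
| 80% vs 70% | 1% | 3% |

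**5. Dependence on the analysed arm sizes, at 0.05/3.** For unequal arms, the first arm listed has the 80% rate.

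| Arms | Fisher maximum size | Power for 80% vs 40%, Fisher → Boschloo |
|---|---|---|
| 15/15 | 0.0057 | 0.303 → 0.446 |
| 15/14 | 0.0089 | 0.355 → 0.406 |
| 14/14 | 0.0061 | 0.257 → 0.391 |
| 14/13 | 0.0098 | 0.303 → 0.362 |
| 13/13 | 0.0071 | 0.271 → 0.337 |
| 13/12 | 0.0112 | 0.323 → 0.358 |
| 12/12 | 0.0068 | 0.235 → 0.282 |

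The rounded threshold matters in some rows. At a literal 0.017, the two tests have the same rejection region at 13/12, so the gain is zero. At 13/13 it is 0.298 → 0.337, and at 12/12 it is 0.235 → 0.351.

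**The case against.** The case for leaving the plan alone is substantial.

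- **Fisher as planned is correct.** It is prespecified and common for small arms, and it bounds the error both conditionally on the margins and unconditionally. Boschloo bounds only the unconditional error, and whether to condition is a long-standing methodological choice. It would therefore be too strong to say that Boschloo gives the same guarantee or that Fisher's conservatism buys nothing. This stands. The counterpoint is that the total number of acceptors is not fixed here, so the unconditional error is a reasonable target.
- **The two-thirds figure belongs to full, equal arms of 15.** Losing one patient from one arm cuts the unused share from 66% to 47% (1 − 0.0089/0.01667). The article plans for dropout, so a general loss of two thirds should not be inferred. This stands.
- **Large power gains need large assumed gaps.** All arms receive the same 4 h/day instruction, so small differences are at least as plausible, and for those both tests have little power. Even 80% vs 40% stays below 50% with Boschloo. This stands: the arm size and the three-way correction are the main limits.
- **Little depends on these tests.** A reader might infer that the choice of test could mislead the selection of an arm for the main trial. The article does not support that. The Verum stimulation and Sham intervention sections tie that choice to the effect on fatigue. Feasibility success is defined by 80% of patients reaching the usage target, without Fisher's test.

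None of this removes the efficiency loss. It limits how much the loss matters.

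**Conclusion.** The point holds as a matter of efficiency. With 15 analysed per arm, each Fisher comparison has a true unconditional error of at most 0.0057 (0.0067 at the printed 0.017) against about 0.0167 allotted. Boschloo's test reaches 0.0165 within the same threshold.

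For 80% vs 40%, the gain at 0.05/3 is about 14 points at 15/15, 13 at 14/14, 7 at 13/13, 5 at 12/12, and 3 to 6 when the arms differ by one. It is zero at 13/12 with a literal 0.017. These gains rest on assumed acceptance rates and on the arm sizes finally analysed, neither of which the article settles.

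The plan contains no error here and no inflation of type I error. The 80% acceptance criterion and the fatigue-based choice of arm are untouched. The change is optional.

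**What to change.** In the Data analysis section, before the data are examined, name Boschloo's two-sided unconditional exact test for the three pairwise comparisons of the binary usage outcome, at the same Bonferroni threshold. Add an unconditional exact confidence interval for each difference in proportions and report Fisher's p beside it. Writing the threshold as 0.05/3 rather than 0.017 would remove the dependence on rounding.

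The cost is one sentence and a different function call in standard software, with no extra patients or data. There are two downsides: the test is less familiar to readers, and it controls the error unconditionally but not conditionally on the margins.

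### Three pairwise Fisher tests at a Bonferroni 0.017 are valid but give up recoverable power, and the text gives the three-group test no role

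*Protocol article*

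**What the plan says.** All statements below are in the protocol article.

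- **Primary outcome.** Data analysis makes it binary ("primary outcome is an incidence rate with patients who exceed a usage-time-threshold") and says that a two-sided Fisher's exact test "will be used to evaluate the difference between the three groups".
- **Status of the pairs.** The next sentence says that "the two treatment groups will be descriptively compared with the placebo group, and between themselves". The same paragraph then counts "in total three two-group comparisons" as the reason for using Fisher's test.
- **Threshold.** From an "overall (studywise) alpha of 0.05", the section concludes that "three tests result in an Bonferroni-adjusted (comparisonwise) threshold of p/ 3 = 0.017" and that "p-values below this threshold denote a statistical significant difference".
- **Continuous outcomes.** Kruskal-Wallis, a three-group test, is named. No pairwise rank test is named for MFI20.
- **Size.** The trial enrols 45 patients, "with 15 assigned to each of the three groups". Sample size calculation uses alpha 0.05, not 0.017, and MFI20 shifts of 5 and 10 units against placebo. It claims 80% power with 12 per arm.

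**The concern.** The same three pairs are described once as descriptive and once as subject to a significance threshold. The three-group test is mentioned, but its result decides nothing. A reader can work out that three Fisher tests at 0.017 are probably meant, but the text should not leave that to be inferred.

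The likely rule also spends less of the allowed error than it needs to. Fisher tests on 15 against 15 are already conservative because they are discrete, and Bonferroni adds to that. The three-group tests the plan already names could act as a gate that releases each pair at the full 0.05.

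This bears most on the comparison of subthreshold stimulation (Verum-1) with sham. The Verum stimulation and Sham intervention sections make the design of later studies depend on whether subthreshold stimulation works.

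**Working it through.** **1. The plan's own figure.** 0.05 / 3 = 0.016667, which is 0.017 at three decimals. The printed value is reproduced. Used literally, 3 × 0.017 = 0.051.

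**2. Why the gate is valid with three arms.** The pairwise nulls are 1=2, 1=3 and 2=3. If any two hold, all three arms are equal, so every intersection of two or more nulls is the global null. A closed test therefore needs only a valid global test at 0.05 and each pair at 0.05. Familywise error is strongly controlled at 0.05. The shortcut does not carry over to four or more arms.

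**3. Primary outcome, exact.** All 16³ = 4,096 outcomes (a, b, c) with 15 per arm were enumerated. Each was weighted by Bin(a; 15, p1) × Bin(b; 15, p2) × Bin(c; 15, p3), and the weights were summed over outcomes where the rule rejects. The printed rule is pairwise two-sided Fisher p < 0.017. The gated rule is Fisher-Freeman-Halton p ≤ 0.05 on the 3×2 table, then pairwise Fisher p ≤ 0.05. The documents give no arm-level rates, so those below are assumptions placed around the 80% acceptance target.

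Familywise error, all arms equal:

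| Common rate | Printed 0.017 | Gated |
|---|---|---|
| 50% | 1.5% | 4.3% |
| 60% | 1.6% | 4.1% |
| 70% | 1.8% | 3.7% |
| 80% | 1.5% | 2.8% |

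When one arm truly differs, the largest error for the remaining true null is 0.7% (printed) against 1.8% (gated).

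Power for one given true pair:

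| Arm rates | Printed 0.017 | Gated | Gain (points) |
|---|---|---|---|
| 80/80/40% | 30.5% | 44.4% | 13.9 |
| 90/90/50% | 39.5% | 52.5% | 13.0 |
| 80/80/60% | 6.0% | 10.3% | 4.3 |

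Power for at least one pair goes from 44.9% to 59.8% (80/80/40%), from 55.5% to 67.9% (90/90/50%) and from 24.5% to 36.1% (80/80/50%). Every outcome rejected at 0.017 is also rejected by the gated rule.

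**4. The gate is needed.** With 12 per arm, as after dropout, pairwise Fisher tests at 0.05 without a gate reach a familywise error of 5.9%. With the gate the maximum is 3.5%.

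**5. MFI20, simulated.** The inputs are normal data and shifts 0/5/10, with Kruskal-Wallis as the gate and pairwise Wilcoxon tests. The Wilcoxon tests are an assumption, since the plan names none. No SD is given. An SD of about 7.25 reproduces the stated 80% if that figure refers to Kruskal-Wallis at 0.05 with 12 per arm. With SD 7.25 at 12 per arm, or SD 8 at 15 per arm, each 5-unit contrast rises from about 19–21% to 32–34%. Power for at least one pair rises by only about 2 to 5 points. Simulated familywise error of the gated rule is 4.8% with all arms equal and 4.6% with one arm different.

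**6. The rounding.** For 15/15 against 9/15, all six non-acceptors fall in one arm. The two-sided Fisher p = 2 × C(15,6) / C(30,6) = 2 × 5,005 / 593,775 = 0.01686. This is below 0.017 but above 0.05/3 = 0.01667.

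**The case against.** The strongest reply is that nothing here is wrong. Bonferroni is standard, pre-specified and keeps familywise error well under 0.05. That stands: a reader might infer that it is the wrong tool, and the documents do not support that.

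Nor does the rounding endanger error control. It makes the rule slightly more liberal, not more conservative, and the largest familywise error at 0.017 is still about 1.8%.

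A reader might also take the gated rule to have the same error rate. Only the 0.05 ceiling is shared; the error actually spent rises, as the first table shows. The low figures for the primary outcome come partly from the discreteness of Fisher's test, and they do not describe MFI20, where error under Bonferroni is already about 3.8%.

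The trial is a pilot. Its success criterion, at least 80% of patients averaging 4 h per day, does not depend on any between-arm test. The 40-point gaps that show the largest gains are assumed, and with a 20-point gap neither rule is useful. This limits the importance of the point without removing it.

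Finally, the text does identify three two-group tests, so it would be too strong to say that no rule can be recovered. What remains is a wording conflict over the status of those tests, and an unused three-group test.

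**Conclusion.** The point holds as a worthwhile, low-cost improvement, not as an error of type I control. For the binary primary outcome at 15 per arm, the gated rule keeps familywise error at or below about 4.3% and loses no Bonferroni rejection. It adds about 13 to 14 points of power for a 40-point difference and about 4 points for a 20-point difference. For MFI20 the benefit lies in the individual 5-unit contrasts and is small for finding any difference at all. These sizes rest on assumed arm rates, on assumed SDs with normal data, and on pairwise rank tests that the plan does not name. Power remains modest under either rule.

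**What to change.** Replace the threshold text in Data analysis with one rule. For each outcome tested in this way, first apply the three-group test at two-sided 0.05: Fisher-Freeman-Halton for the binary primary outcome, Kruskal-Wallis for MFI20. Only if it is significant, test the three pairs, each at two-sided 0.05, and name the pairwise test for MFI20. Delete the 0.017 threshold, and do not call these comparisons descriptive.

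If Bonferroni is kept, write the threshold as 0.05/3 and still remove the conflict over whether the pairs are descriptive.

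The change needs no extra patients or data and should be made before unblinded analysis. It has two downsides. No pairwise claim is possible without a significant three-group test, which costs nothing on the primary outcome at 15 per arm and a negligible amount for MFI20. Unadjusted pairwise 95% intervals would not be simultaneous; the plan already reports 95% intervals beside a 0.017 threshold, so one sentence saying so is enough.
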